### Intervention

#### Transition programme (intervention group)

This study implements a multicomponent intervention, adapted from a brief transition programme developed by Hilderson *et al*.^23^ Adaptation of the programme followed the intervention mapping process.^24^ Intervention mapping is a thorough method used to build comprehensive programmes for health promotion and consists of six consecutive steps: (1) assessment of the needs of the target population; (2) defining programme objectives by specifying performance and change objectives; (3) determining theory-based intervention methods and practical strategies; (4) designing and producing the intervention programme; (5) adoption and implementation of the intervention; and (6) developing and executing a plan for evaluation.^24^ Applying the intervention mapping method in this study ensures that the intervention is well-grounded and includes the necessary components to target the programme objectives. A detailed description of each of the steps will be given in a related article.

The transition programme includes eight key components: (1) a TC; (2) a written person-centred transition plan; (3) provision of information and education about the condition, treatment and health behaviours; (4) availability by telephone and email; (5) information about and contact with the Grown-Up Congenital Heart Disease (GUCH) clinic; (6) guidance of parents; (7) meeting with peers; and (8) the actual transfer to the GUCH clinic.

These components are implemented in five steps: (1) a first patient visit with the TC; (2) a second outpatient visit with the TC; (3) information day for adolescents and their parents; (4) a third outpatient visit with the TC; and (5) actual transfer to the GUCH clinic. The TCs are specialised nurses at the outpatient clinic of paediatric cardiology who have received specific training in performing this intervention.

Throughout the intervention, the TCs employ a PCC approach. PCC implies that participants are active agents in their care and decision-making process.^12^ Ekman *et al*^12^ proposes that PCC can be implemented in three stages. First, initiating the partnership by allowing the patients to tell their story (patient narratives). This allows for the patients' views to be at the centre of care. Second, developing the partnership through constant communication between the patient and healthcare providers. This is accomplished by sharing experiences and building a common understanding of the care plan. Third, safeguarding the partnership by documenting the decisions made and the preferences of the patients.

The content of the visits is individualised, age and developmentally adapted, and it is documented in the individualised transfer plan. The TCs, together with the adolescent, are in charge of determining which topics are important to discuss, in establishing goals related to patient empowerment and in assessing the need for referral to other services.

#### Usual care (intervention, control and comparison group)

All adolescents who participate in the study receive usual care, irrespective of whether in the intervention, comparison or control group. Usual care includes visits to an outpatient paediatric cardiology clinic where they meet a nurse and a paediatric cardiologist. Disease complexity determines the frequency of the visits. None of the participating centres have a TC as a part of usual care and there is no documentation of transition plans. It is common practice in Sweden that patients are transferred to adult care around the age of 18 years.

Since usual care can vary across clinics and over time, an assessment of transition-related practices will be carried out in all the centres at the beginning of the intervention and at the end of the study. This assessment will comprise three elements: (1) a structured survey called CHAT (Congenital Heart Adolescent and Transition; on file); (2) interviews with healthcare professionals who are involved in the care for adolescents with CHD in the participating centres and (3) observations of the routine during the clinic visits.

### Blinding

Owing to the nature of the intervention and the study design, it is not possible to blind the participants, TCs or DCOs. However, the TCs and DCOs in charge of carrying out the intervention and data collection are not involved in the preparation of the intervention design or in the statistical analyses.

To avoid cross-contamination between the comparison and the intervention group within the RCT centres, TCs are not involved in the delivery of care of the comparison group and other healthcare professionals in the participating centres will not be informed of the intervention components. DCOs in the control group do not participate in discussions of the intervention.

### Intervention fidelity

To ensure that the transition programme is implemented according to the developed intervention, the TCs are selected based on their experience of working with children and adolescents with CHD. In preparation for this study, they received a specifically designed 4 days training programme, addressing adolescents' health and development; communicating with and interviewing young persons; patient education; PCC; and the detection of and screening for risk behaviours. Training is given by experts in the aforementioned fields and features different pedagogical approaches, for example, group discussions, case assessments and role play. In addition, the TCs were asked to read two textbooks on adolescent health and PCC.

Standard operating procedures (SOPs) for each group of the study were developed in order to ensure consistency throughout the study. These SOPs included: ethical approval; study preparation; study administration; participants recruitment and survey completion; intervention characteristics; usual care; data storage, entry and security; study progress; and publication policy.

Intervention fidelity is monitored as part of the process evaluation. The Medical Research Council (MRC) guidance on process evaluation of complex interventions is applied,^25^ and both quantitative and qualitative methods will be used. In the quantitative assessment, we investigate the acceptability, adherence/fidelity and attrition, as well as potential safety issues. These data are collected using three assessment forms (enrolment/follow-up form, adverse events (AEs) report and intervention implementation form) filled out by the TCs during the intervention period. The qualitative assessment will obtain information about the experiences of and implementation by the TCs and will provide insights into the mechanisms of impact based on the experiences of patients and their parents. The process evaluation will be undertaken as a separate study conducted in parallel with this effectiveness study.

### Follow-up period and data collection

During the 2-year follow-up period, outcome measurements are assessed on three different occasions: T0, baseline when the participants are 16 years old; T1, midterm when the participants are 17 years; and T2, final data collection when the participants have been transferred to adult care and are ∼18.5–19 years old (see figure 1).

Participants from the intervention group will be mailed the set of questionnaires 1 month before the outpatient clinic visit. If the questionnaires have not been received by the time of the visit, they will have the opportunity to complete them while waiting for their appointment. Patients from the control and comparison groups may not have a scheduled outpatient visit. Therefore, data collection in these groups is completely undertaken by post when the participants are 16 (T0), 17 (T1) and 18.5 years old (T2).

To minimise non-response in the comparison and control groups, a modified Dillman procedure will be used.^26^ Two weeks after the documents are sent, non-responders will receive a first personalised reminder in the form of a text message. If after 4 weeks the questionnaires have not been received, a reminder letter and a new set of questionnaires is sent. After 6 weeks, persistent non-responders are contacted by telephone and asked whether they received the questionnaires, if the mailing address is correct, if they want a new set of questionnaires and if they want to continue participating in the study. After 8 weeks, a last reminder is sent to those who agree to participate in the study during the telephone call.

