### Sample size estimation

Sample size calculation is based on the primary outcome of patient empowerment. The target is an improved patient empowerment score of 5.25 points on a scale from 15 to 75 (ie, 0.5 SD). For two-sided tests with α=0.05 and power=80%, 63 patients are needed in each arm of the RCT. In order to compensate for a potential 10% dropout rate, we will recruit 70 patients in each arm of the RCT. An additional 70 patients will be recruited in the centres of the control group. Among the four centres, a total of 210 patients will be enrolled (see figure 1).

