### Randomisation

Using a web-based system, a stratified block randomisation with a random variable block size will assign patients of the RCT centres to the intervention group or the comparison group (1:1).^21^ Block randomisation ensures that the TCs in the two centres have a relatively continuous exposure to the intervention over time, which allows them to keep their skills up to date and to ensure the fidelity of the intervention. The fact that the block sizes vary randomly minimises the possibility that the TCs could predict group assignments.

Stratification is made by centre and disease complexity. The stratification for centre ensures that the two centres have an equal number of intervention patients. Stratification by disease complexity (mild; moderate; complex)^22^ is important to avoid over-representation of those people with, for example, complex CHD in one or the other group due to failing randomisation.

Overall, this approach decreases the within-centres variability and reduces the risk for bias and confounding.^21^ The TCs are responsible for accessing the randomisation system in order to determine patient allocation.

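### Timing, completion setting and reminders for the self-reported GYPES differ between the two randomised arms, which can mix measurement or non-response artefact into the primary comparison

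*Protocol article*

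**What the plan says.** All of this is in the protocol article.

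- **Intervention arm, timing and setting** (Follow-up period and data collection): "Participants from the intervention group will be mailed the set of questionnaires 1 month before the outpatient clinic visit". If the set has not come back by the visit, the patient may complete it while waiting for the appointment.
- **Comparison arm and control group** (same section): because these patients may have no scheduled visit, "Therefore, data collection in these groups is completely undertaken by post when the participants are 16 (T0), 17 (T1) and 18.5 years old (T2").
- **Reminders** (same section): "To minimise non-response in the comparison and control groups, a modified Dillman procedure will be used". The steps are a text message at 2 weeks, a letter with a new set at 4, a telephone call at 6 and a last reminder at 8. No reminder is described for the intervention arm.
- **T2** (same section): for the whole study, "final data collection when the participants have been transferred to adult care", at about 18.5–19 years.
- **Allocation** (Randomisation): a web-based system "will assign patients of the RCT centres to the intervention group or the comparison group (1:1").
- **Outcome and blinding** (Primary outcome measures; Blinding): GYPES is the sum of 15 self-completed Likert items. Participants, transition coordinators (TCs) and data collection officers are not blinded.
- **Analysis** (Statistical analyses plan): an unadjusted permutation test between two groups. A complementary analysis of covariance adjusts for baseline variables that differ significantly and for centre.

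**The concern.** Randomisation makes the arms comparable at entry. It does not protect a comparison in which the outcome is then collected under arm-specific rules. Three features follow allocation here: what triggers the mailing (a visit or a birthday), where the form may be completed, and how hard a non-responder is pursued. A fourth, age at T2, may follow it too.

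For an unblinded self-report score, each of these could shift the recorded mean or change who contributes data. The visit trigger matters most for missing data. As written, a comparison patient with no visit still receives the mailing and up to four follow-up steps. The text states no equivalent for an intervention patient without a visit. The postal schedule also includes T0, so the difference may reach the baseline score and weaken baseline adjustment.

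At stake is the only randomised comparison of the primary outcome. Because these features coincide with arm, an analysis planned later can probe them but cannot cleanly separate them from the programme effect.

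**Working it through.** **1. The plan's own figure.** Inputs from Sample size estimation: "The target is an improved patient empowerment score of 5.25 points on a scale from 15 to 75 (ie, 0.5 SD"), and "For two-sided tests with α=0.05 and power=80%, 63 patients are needed in each arm of the RCT". The implied SD is 5.25 / 0.5 = 10.5 points.

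n per arm = 2 × (1.96 + 0.8416)² × (10.5 / 5.25)² = 2 × 7.849 × 4 = 62.8, so 63. Power at 63 per arm is 80.1% by the normal formula and 79.5% by the noncentral t. Allowing for dropout, 63 / 0.90 = 70, in line with "compensate for a potential 10% dropout rate, we will recruit 70 patients in each arm of the RCT". The figures reproduce, and nothing here disputes them.

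**2. Arms side by side.**

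| Feature | Intervention | Comparison |
|---|---|---|
| First delivery | Mailed | Mailed |
| Trigger | One month before a clinic visit | Ages 16, 17 and 18.5 |
| Place of completion | By post, waiting room as fallback | By post only |
| Reminders stated | None | 2, 4, 6 and 8 weeks |
| T2 age | Study-wide 18.5–19, linked to a visit | 18.5 |

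Nominal ages agree at T0 and T1. At T2 the largest implied gap is 19 − 18.5 = 0.5 year.

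**3. What a given artefact would do.** The size is not in the documents, so the values of b below are assumptions.

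SE of the difference = 10.5 × √(2/63) = 1.87 points.

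Rejection rate with no programme effect and an arm-wide artefact of b points = Φ(b/SE − 1.96) + Φ(−b/SE − 1.96), a normal approximation to the permutation test.

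| b (points) | Share of 5.25 | Rejection rate |
|---|---|---|
| 0 | 0% | 5.0% |
| 0.5 | 10% | 5.8% |
| 1 | 19% | 8.3% |
| 2 | 38% | 18.8% |

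**4. Age at T2 alone.** Assume GYPES drifts by 0.5 to 3 points per year and the gap is 0.25 to 0.5 year. Then b runs from 0.5 × 0.25 = 0.125 to 3 × 0.5 = 1.5 points, and the rejection rate from 5.1% to 12.6%. With drift of at most 1 point per year, b is at most 0.5 and the rate at most 5.8%.

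**5. Unequal response alone.** Assume response differs by 10 percentage points between arms and non-responders differ from responders by 0.5 SD. The bias is 0.10 × 5.25 = 0.525 points, about the same as the 0.5-point row. Power for the target changes little: 80% with 5% against 15% missing, and 78% with 10% against 20%.

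**The case against.** The asymmetry has a stated reason: comparison and control patients may have no visit, so reminders replace the waiting room as a way of catching late forms. That explains postal collection in those groups. It does not stop the same schedule and reminders being used in the intervention arm.

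Several stronger readings are tempting, and the documents do not support them:

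- **The arms use different routes throughout.** Both are mailed the same self-completed questionnaires, and the waiting room is only a fallback. An assumed setting effect of 0.1–0.2 SD (1.05–2.1 points) should therefore not be applied to the whole arm. If 20–30% of patients used the fallback (also an assumption), the arm mean would move by about 0.2 × 1.05 = 0.2 to 0.3 × 2.1 = 0.6 points, and the rejection rate would be about 5.1–6.3%.
- **The arms are assessed at different ages.** T0 and T1 match nominally. The 18.5–19 window is study-wide and contains the postal age of 18.5; no T2 age is given for the intervention arm alone.
- **Intervention patients who disengage are lost, and the bias favours the programme.** No passage says they go unpursued. Standard operating procedures for each group cover survey completion and are not shown. The direction is unknown.
- **Forms pass through the TC.** TCs enter data, but return through the TC is not stated, and records are checked against raw data at least twice a year.

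What stands is that the published text itself assigns a visit trigger to one randomised arm and names reminders only for the other. This is stated text, not detail left to a fuller plan. The limitations in the Discussion mention lack of blinding but not this difference.

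**Conclusion.** The concern holds as a possible, avoidable source of bias. Timing, completion setting and stated pursuit of non-responders follow allocation, and age at T2 may differ by up to about half a year. Neither the unadjusted test nor adjustment for imbalanced baseline variables and centre addresses differences that arise after randomisation.

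Size and sign cannot be derived from the documents. The 6%, 8% and 19% rejection rates for 0.5, 1 and 2 points are illustrations. They assume SD 10.5, 63 evaluable per arm, no programme effect and an artefact spread over the whole arm. An effect confined to waiting-room completion would probably sit near the bottom of that range, and so would a T2 age gap unless GYPES drifts steeply. A reader might infer that the primary result would be invalid or inflated in the programme's favour; the text does not support that. The case for acting is that the remedy is cheap and the difference cannot be removed once the data are collected.

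**What to change.** Amend the section on follow-up and data collection as follows:

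1. Mail the questionnaires to both randomised arms and the control group on the same age-based schedule, with one common T2 age window that does not depend on a clinic visit or on having transferred.
2. Apply the same modified Dillman reminders to every non-responder in all groups.
3. Keep waiting-room completion as a fallback if wanted, but record the place and date of completion for every form.
4. Add a sensitivity analysis for age at T2 and completion setting. It supports the common procedure but does not replace it, because both variables are tied to arm.

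The cost is postage and reminders for about 70 more patients and a small change to the operating procedures. The sample size stays at 63 evaluable and 70 recruited per arm.

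When the article appeared in April 2017 there was still time for T2. Recruitment at age 16 began in July 2016, so even a patient then just under 17 would reach 18.5 only about January 2018. Some T0 and T1 forms may already have been collected under the split rules, and their setting and date should be recovered where possible.

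### Questionnaire route and reminders are set by randomised arm from T0 onwards, which implies that baseline is collected with allocation known; the composite end point and the complementary ANCOVA are exposed

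*Protocol article*

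**What the plan says.** Under Follow-up period and data collection, the first assessment is "T0, baseline when the participants are 16 years old"; its timing relative to randomisation is not given. The same section then describes the route by arm:

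- **Intervention:** "Participants from the intervention group will be mailed the set of questionnaires 1 month before the outpatient clinic visit". If the forms are not back by the visit, "they will have the opportunity to complete them while waiting for their appointment". No exception is made for T0.
- **Comparison and control:** "Patients from the control and comparison groups may not have a scheduled outpatient visit", and their data collection is therefore "completely undertaken by post when the participants are 16 (T0"), and likewise at T1 (age 17) and T2 (age 18.5).
- **Reminders:** "To minimise non-response in the comparison and control groups, a modified Dillman procedure will be used". It runs from a text message at 2 weeks to a last reminder at 8 weeks. At 6 weeks, non-responders are asked, among other things, whether they wish to stay in the study. Nothing comparable is described for the intervention arm.

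Under Randomisation, RCT-centre patients are allocated individually 1:1, and "The TCs are responsible for accessing the randomisation system in order to determine patient allocation". A completed T0 is not made a condition. Under Blinding, participants, transition coordinators (TCs) and data collection officers are all unblinded.

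Baseline is used in two places. The composite end point (under Parental uncertainty) classifies a patient as improved if any of five outcomes has risen by 0.5 SD from that patient's own baseline. The complementary ANCOVA (Statistical analyses plan) adjusts for centre and for baseline variables that differ significantly between groups. The primary test of empowerment level is an unadjusted permutation test.

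**The concern.** Two patients at the same RCT centre can be sent down different T0 routes, one as intervention and one as comparison, only if their allocation is already known. Taken literally, the text therefore places a self-reported baseline after an unblinded allocation. Knowledge of allocation, the setting, the timing (tied to a visit or to age) and different follow-up of non-responders could then each move T0 scores apart between the arms, or change who returns them.

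A T0 score obtained in this way is no longer a pre-randomisation measurement. The composite uses it as each patient's reference value. The ANCOVA rule picks covariates because they differ between arms, so it would tend to select a variable that allocation itself had shifted.

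**Working it through.** **1. Does the text imply that allocation is known at T0?**
- The comparison group's postal route names T0 explicitly.
- The intervention route is described without excluding T0.
- Both groups come from the same two centres by individual randomisation, so centre does not determine the route; only allocation does.
- Nothing in the article puts T0 before randomisation.

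The inference is sound for the two randomised arms. It does not extend to the intervention-naïve control group, which is defined by centre. There, the postal route is only a difference in mode.

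**2. The plan's own figure.** From Sample size estimation, 5.25 points = 0.5 SD, so SD = 5.25/0.5 = 10.5. Then n = 2 × (1.960 + 0.842)² / 0.5² = 62.8, i.e. 63 per arm; with 10% dropout, 63/0.9 = 70. Both stated figures are reproduced, and the point does not change them.

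**3. Sensitivity to a T0 shift.** The protocol gives neither a shift nor a T0–T2 correlation, so both are assumed: s = 0.1 to 0.3 SD upwards in the intervention arm at T0 only, and ρ = 0.3 to 0.7, with 63 per arm.

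- *Chance that baseline GYPES is selected for the ANCOVA.* The SE of the T0 difference is 10.5 × √(2/63) = 1.87 points. The chance of p ≤ 0.05 is Φ(d/1.87 − 1.96) + Φ(−d/1.87 − 1.96) for a shift of d points. This gives 8% at 1 point and 19% at 2 points.
- *ANCOVA estimate if it is selected.* Expected estimate = (0.5 − ρs) × 10.5 when the true effect is 0.5 SD.
- *One composite component, no true change.* The SD of change is √(2(1 − ρ)), which is 1 at ρ = 0.5. P(improved) = 1 − Φ(0.5 + s).

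| s (SD) | points | selected for ANCOVA | ANCOVA estimate if selected, ρ = 0.3 / 0.5 / 0.7 | one component improved, ρ = 0.5 |
|---|---|---|---|---|
| 0 | 0 | 5% | 5.25 | 31% |
| 0.1 | 1.05 | 9% | 4.93 / 4.73 / 4.51 | 27% |
| 0.2 | 2.10 | 20% | 4.62 / 4.20 / 3.78 | 24% |
| 0.3 | 3.15 | 39% | 4.31 / 3.67 / 3.05 | 21% |

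A downward shift acts in the opposite direction. At s = −0.2 and ρ = 0.5 the ANCOVA estimate is (0.5 + 0.1) × 10.5 = 6.30 points, and the component is met with probability 1 − Φ(0.3) = 38%.

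**4. Primary test.** Read as a comparison of T2 level, it contains no T0 term. With 63 per arm its power stays at 0.80 whatever the T0 shift.

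**The case against.** The order is inferred. The sentence on the intervention route does not itself name T0, Figure 1 is not shown, and the SOPs, which cover recruitment and survey completion, may well put T0 first. This stands as a limit on certainty. If the SOPs do so, however, the article's section misdescribes the trial and should be corrected.

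The contrast in routes is also modest. Intervention forms are mailed too, and the waiting room is only a fallback. What remains different is the fallback, the timing and the reminders. In addition, the same arm-specific routes apply at later assessments, so a mode effect that is constant at T0 and T2 would largely cancel in change. Both objections stand, and the table applies only to a shift confined to T0.

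Several stronger readings are tempting but not supported:

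- *The primary result is biased.* Read as a T2 comparison, the unadjusted test needs no T0 value. It would be exposed only if it were run on change.
- *A 1 to 2 point shift biases the effect by 19% to 38% of the target.* That is the arithmetic for a mean change score (1/5.25 and 2/5.25), and no such analysis is planned.
- *The ANCOVA is always biased.* Baseline GYPES enters only if it differs significantly.
- *Intention to treat is broken.* Nothing in the article drops patients who do not return T0.
- *The programme's content has already acted on T0.* Intervention forms are due before the visit or while waiting for it. Knowledge of allocation, the setting, timing and selective return are the plausible mechanisms.

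**Conclusion.** The point holds in limited form. As written, the article makes T0 route and reminders depend on randomised arm in an unblinded trial, which implies that allocation is known when T0 is collected. The consequence reaches the composite end point and the complementary ANCOVA.

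Neither the size nor the direction of any shift can be determined from the article. Under the assumed T0-only shifts of 0.1 to 0.3 SD, one composite component moves by about 3 to 10 percentage points at ρ = 0.5 (31% to 27%, or to 21%). An ANCOVA that selects baseline GYPES gives 4.93 to 3.05 points where 5.25 is true. These figures show sensitivity and do not estimate an actual bias. The change is worth making because it is cheap and removes this route to bias for patients still to be enrolled.

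**What to change.** For RCT-centre patients still to be enrolled, fix the order: consent, T0 by the same route with the same reminders for everyone, receipt logged, randomisation. Have the web system refuse to randomise until T0 is recorded. Reword Randomisation and Follow-up period and data collection so that they agree on this order.

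For patients already randomised (recruitment began in July 2016 and was ongoing at submission):

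- log the date and mode of T0 relative to allocation;
- keep every randomised patient in the T2 comparison;
- treat results that depend on baseline, meaning the composite and any ANCOVA using T0 patient-reported scores, as supportive;
- report alongside them an ANCOVA adjusted only for centre and disease complexity, the two stratification factors, which are fixed before randomisation.

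A sensitivity analysis that excludes T0 values completed after allocation is not advisable. It could discard most T0 data, or select patients on a variable related to arm.

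Cost: an SOP amendment and one entry check in the randomisation system. The wait between consent and allocation could reach about 8 weeks, the length of the reminder schedule, and patients who do not return T0 would not be randomised. The targets of 63 evaluable and 70 recruited per arm are unchanged.

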### Objective and hypothesis

This article describes the protocol for a study to test the effectiveness of a transition programme to empower adolescents with CHD in the transition to adulthood and the transfer to adult care. The main hypothesis is that adolescents with CHD who receive a structured, person-centred transition programme over a 2-year period have a higher patient empowerment score than adolescents receiving usual care.

This study is presented in accordance with the guidelines issued by SPIRIT for reporting of study protocols.^19^

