### Participants and recruitment

Eligible participants are (1) adolescents with CHD, defined as “a gross structural abnormality of the heart or the intrathoracic great vessels that is actually or potentially of functional significance”;^20^ (2) age 16 years; (3) Swedish speaking and (4) literate.

Patients are excluded if they do not have the physical or cognitive capacity to complete the questionnaires, or have acquired heart conditions or heart transplantation. Parents of the adolescents will also be asked to participate. All eligible participants are recruited by a transition coordinator (TC) or a data collection officer (DCO).

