Second, the proposed hybrid experimental design allows us to account for potential contamination of the control group. Indeed, the three arms allow performance of direct comparison between the intervention and comparison group while enabling a comparison of findings with those obtained in intervention-naive centres.

Third, patient empowerment is used as the primary outcome. Empowerment is argued to be important for the development and application of skills to promote behavioural changes in the adolescents.^10^ Admittedly, empowerment can be seen both as a process and an outcome.^10^ However, being an intermediate outcome, empowerment can be argued to be proximal to the intervention, whereas continuing cardiac care, reduced morbidity or mortality are probably the ultimate, but more distal outcomes.

Fourth, the PCC approach that is used throughout the transition programme is an important asset in the process of empowering patients.^11^ Providing transitional care from a person-centred perspective is novel and has not been evaluated before in this age group.

Fifth, we follow-up the patients for more than 2 years. While doing so, we substantially expand the follow-up period of 12 months as used in prior studies.^7^

Sixth, since usual care may vary across centres and over time, we carry out a formal usual care assessment. Such a usual care assessment is important to draw firm conclusions, and yet this is seldom performed in clinical trials.^50^

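### Assessments set by age, with entry at any point during age 16, allow 1.5 to 2.5 years of postal follow-up, so the claimed follow-up beyond 2 years is not assured, and T2 timing differs between the RCT arms

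*Protocol article*

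**What the plan says.** All statements are in the protocol article.

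- **Entry.** Participants and recruitment gives the age criterion as "2) age 16 years; (3) Swedish speaking", with no narrower window.
- **Assessments, all groups.** Follow-up period and data collection describes a 2-year follow-up with "T0, baseline when the participants are 16 years old; T1, midterm when the participants are 17 years". T2 is "final data collection when the participants have been transferred to adult care and are" about 18.5–19 years old.
- **Assessments by group.** The same section says "Participants from the intervention group will be mailed the set of questionnaires 1 month before the outpatient clinic visit". The comparison and control groups, who may have no scheduled visit, are assessed "by post when the participants are 16 (T0), 17 (T1) and 18.5 years old (T2".
- **Follow-up claim.** The Discussion lists as a strength that "we follow-up the patients for more than 2 years", against a 12-month maximum in prior studies.
- **Programme length.** The hypothesis concerns adolescents "who receive a structured, person-centred transition programme over a 2-year period". The last of the programme's five steps is the actual transfer, and under Usual care "patients are transferred to adult care around the age of 18 years".
- **Calendar.** Trial duration gives recruitment from July 2016 to December 2017, with data collection expected to finish by December 2019.

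**The concern.** Entry, assessment and transfer are each tied to age, while the follow-up and the programme are described in years. The two agree only if everyone enters at nearly the same age. Entry spread over the year of age 16 makes time from baseline to T2 vary by up to a year in the postal groups, and some patients may have less than the length presented as an advance on earlier studies.

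The arms of the RCT also follow different scheduling rules. Intervention questionnaires are linked to clinic visits, with T2 somewhere in the 18.5–19 range. Comparison questionnaires are posted at 18.5. The primary comparison could then set scores taken at different ages and different times since randomisation against each other. Randomisation does not protect against this, because the timing rule depends on the arm.

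**Working it through.** **Inputs.** Entry age *a* is from 16.0 to just under 17.0 (Participants and recruitment). T2 is at 18.5 in the postal groups and about 18.5–19 in the general statement (Follow-up period and data collection). Transfer is at about 18 (Usual care). Recruitment takes 18 months from July 2016, and data collection closes 42 months after July 2016 (Trial duration). The distribution of *a* is not given, so every share below rests on an assumed one.

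**1. The plan's own figures.** Follow-up = T2 age − *a*. With T2 at 18.5:
- *a* = 16.0 gives 2.5 years
- *a* = 16.5 gives 2.0 years
- *a* just under 17 gives 1.5 years

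With *a* uniform over the year, the mean is 18.5 − 16.5 = 2.0 years. The Methods' 2 years is therefore reproduced as an average under that assumption. The Discussion's figure is reproduced for every patient only if all enter before 16.5.

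**2. Share at 2 years or less, and the calendar.** Follow-up is 2 years or less when *a* ≥ T2 age − 2. A patient recruited in month *s* (0–18, uniform) reaches 18.5 after data collection closes when *s* + 12(18.5 − *a*) > 42.

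| Entry age (assumed uniform) | Follow-up to 18.5 | At 2 years or less | Reach 18.5 after December 2019 |
|---|---|---|---|
| 16.0 only | 2.5 y | 0% | 33% |
| 16.0–16.25 | 2.25–2.5 y | 0% | 25% |
| 16.0–16.5 | 2.0–2.5 y | 0% | 17% |
| 16.0–17.0 | 1.5–2.5 y | 50% | 8% |

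First row: *s* + 30 > 42 needs *s* > 12, which is 6 of 18 months. Last row: with *u* = 12(*a* − 16), the condition is *s* − *u* > 12, and (6 × 6 / 2) / (18 × 12) = 18/216 = 8%.

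The result is sensitive to T2 age. With uniform entry over the year, the share at 2 years or less is 50% for T2 at 18.5, 25% for T2 at 18.75 or spread evenly over 18.5–19, and 0% for T2 at 19.

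**3. Calendar alone.** Available time is 42 − *s* months, which is 42 − 18 = 24 for the last recruits whatever their age.

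**4. Difference between arms.** T2 up to 19 in the intervention group against 18.5 in the comparison group gives a difference of up to 19 − 18.5 = 0.5 years.

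**5. Programme length.** Entry to transfer at 18 is 18 − *a*, or 1.0–2.0 years. Two years is reached only by entry at the 16th birthday or transfer after 18.

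**6. Sample size.** With 0.5 SD, two-sided α = 0.05 and 80% power, n = 2(1.96 + 0.84)²/0.5² ≈ 62.7, or 63 per arm, and 63/0.9 = 70. Both figures reproduce, and nothing above changes them.

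**The case against.** The case for leaving the schedule alone has force.

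- **Age anchoring is defensible.** Transfer is age-driven, T2 must follow it, and empowerment may change with maturity. This stands, and the fix keeps 18.5 as a floor for T2.
- **Windows may be in the standard operating procedures**, which cover recruitment and survey completion and are not shown. This also stands: a missing window in an article is no finding. But an undisclosed window does not reconcile the stated ages, lengths and dates. Entry confined to the first half of the year rescues the 2 years, yet still puts 17% past December 2019.
- **Entry age precedes randomisation**, so variation from that source does not bias the randomised contrast, and age is recorded. Correct. The visit-linked versus postal T2 is a separate matter.
- **December 2019 is an expectation**, and the Discussion foresees a possible extension. True, so the calendar conflict can be resolved by moving the date.

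A reader might infer three stronger things that the documents do not support:

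- *That half the patients fall short of 2 years.* This needs uniform entry and T2 at exactly 18.5. No entry-age distribution is given, and the share is 0% under other plausible readings.
- *That T1 commonly falls weeks after baseline.* This reads 16 as a whole year but 17 as a birthday. If both are birthdays, the gap is 12 months. If both are whole years with even spread, the mean gap is 12 months, with 3% under 3 months and 0.3% under 1 month.
- *That shorter exposure lowers power.* This assumes benefit proportional to months in the programme. The programme is defined by five steps, and nothing shows that a later entrant misses one. The postal sentence also concerns groups that do not receive the programme.

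**Conclusion.** The point holds as a conflict between stated rules, of minor to moderate weight. Under the stated entry age and the postal T2, follow-up can lie anywhere from 1.5 to 2.5 years, and the proportion at 2 years or less cannot be determined from the article. The Discussion's claim is not assured, does not match the 2 years in the Methods, and cannot hold for the last recruits unless data collection runs past December 2019.

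No single reading satisfies every statement. Birthday entry delivers the follow-up but overruns the calendar for about a third, assuming even recruitment. Entry across the whole year largely fits the calendar but lets follow-up fall below 2 years. The 2-year programme likewise fits only loosely with transfer at about 18.

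The part that bears on the primary comparison is the arm-dependent T2. It can differ by up to about 6 months. Its actual size and the direction of any effect are unknown.

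**What to change.** **Preferred.** Schedule questionnaires by time since randomisation, identically in both RCT arms, and by time since enrolment in the control group: T1 at 12 months, and T2 at the later of age 18.5 and 24 months. T1 then falls during age 17, and T2 at max(18.5, *a* + 2), which is 18.5–19.0, within the ages already stated. Follow-up becomes 2.0–2.5 years for everyone, so the Discussion should say at least 2 years.

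**Cost.** Some intervention-arm questionnaires must be mailed independently of clinic visits. T2 moves later by up to 6 months for patients who enter after 16.5. The latest due date does not move: entry at 16.0 in December 2017 already implies T2 in June 2020 (30 months). The end of data collection should be reset to allow for this and for the 8-week reminder sequence, since even a 24-month T2 for December 2017 recruits falls due in December 2019.

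**Alternative.** Keep the age rule, restate postal follow-up as about 1.5–2.5 years, and use the same T2 timing rule in both RCT arms.

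**In either case**, reconcile the 2-year programme in Objective and hypothesis, the transfer age under Usual care, the follow-up wording in Follow-up period and data collection and in the Discussion, and the end date in Trial duration. How the programme length and the transfer age are reconciled is for the investigators to decide.
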